### Procedures/Interventions

#### Assessment and testing at the Hospital for Sick Children

Prior to receiving intervention, all participants will be asked to attend a half-day medical assessment at the Hospital for Sick Children in Toronto at the beginning and end of the study (6 months after their baseline testing). This testing will be carried out in the clinical investigation unit (CIU) and the exercise laboratory, by trained personnel. Clients will undergo a series of physiological tests in order to assess their metabolic health and physical functioning. Specific elements to be measured include: body composition (body fat percentage), body mass index calculation (weight[kg]/height[m^2^], waist circumference, metabolic profile (including oral glucose tolerance test to screen for diabetes, fasting lipid profile, hepatic enzyme profile [to screen for nonalcoholic fatty liver disease], measurement of various adipokines known to be associated with obesity [leptin, adiponectin, highly sensitive c-reactive protein], blood pressure assessment), fitness level (calculated as VO2 max with testing on a cycle ergometer) and nutritional assessment (using a pediatric-validated food frequency questionnaire) ***(See Appendix A for detailed assessment plan)***. All of these measures have been performed routinely as part of the HISTORY "Determinants of metabolic risk" study. This protocol is performed on a single day, with participants arriving at 8 am and finishing by 2 pm. In the event that subjects decline this medical testing, they will not be excluded from participating in the MI part of the study.

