#### Sample Size and Outcomes (Table 2)

The primary outcome for this study will be the total self-efficacy score as measured in the Child Dietary Self-Efficacy Scale (CDSS) [30]. Previous studies [38] have shown that the mean CDSS total self-efficacy score at in this population (without any intervention) varies between 5.0 and 6.5 with a standard deviation between 0.5 and 1.4. Previous behaviour studies in this population have shown treatment change in CDSS total self-efficacy scores between 1.1 and 1.9. Based on these preliminary data, assuming no differences between groups at baseline and a standard deviation of 1.0 (no differences between groups) we estimates that a sample size of 16 patients per group would allow the detection of between-group differences of 1.5 units with a standard deviation of 1.0 at an alpha level of 0.05 and 80% power. This estimate needs to be inflated to 20 patients per group in order to account for a 20% attrition rate.

**Table 2 T2:** Analysis of Power

	EF = 1.25	EF = 1.5	EF = 1.75
Power			
80%	22	16	10
85%	26	18	12
90%	28	20	14

With this sample size we would be able to detect a difference of 1.4% in BMI percentile between groups over time assuming a 1.5% standard deviation, a difference of 2.85 points in self-esteem as measured in the Rosenberg scale (assuming a 3.15 points standard deviation and a difference of 6.5 points in the CDI depression scale (assuming a 7.1 points standard deviation). In linear regression models using maximum likelihood algorithm for parameter estimation (4 variables per observation in treatment group), this sample size would allow adjusting for 3 independent variables in addition to treatment group.

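### The detectable differences given for BMI percentile, self-esteem and depression match 20 analysed per group, although the plan's own 20% attrition leaves 16

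*Protocol article*

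**What the plan says.** All the figures are in the Protocol article, Sample Size and Outcomes (Table 2). For the primary outcome, the CDSS total self-efficacy score, the section finds that "a sample size of 16 patients per group would allow the detection of between-group differences of 1.5 units". That calculation takes an SD of 1.0, alpha 0.05 and power of 80%. The section continues: "This estimate needs to be inflated to 20 patients per group in order to account for a 20% attrition rate".

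The next paragraph turns to other outcomes: "With this sample size we would be able to detect a difference of 1.4% in BMI percentile between groups over time", with an assumed SD of 1.5. In the same sentence it gives 2.85 points on the Rosenberg self-esteem scale (SD 3.15) and 6.5 points on the CDI depression scale (SD 7.1).

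That sentence does not say whether the sample size meant is 16 or 20 per group. It restates neither power nor alpha, and no part of the document states whether tests are one- or two-sided.

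**The concern.** The only purpose of the 20 is to leave 16 after losses. If the secondary figures rest on 20 analysed patients per group, the attrition allowance has been applied to the primary outcome and dropped for the others within one section.

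What is at stake is how a null result is read. Self-esteem and depression belong to the third hypothesis and BMI to the fourth. A reader who finds no difference would take it that effects of the printed size had a 20% chance of being missed. If 16 per group are analysed, that chance is nearer 28-30%.

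**Working it through.** **Inputs from the document.** 16 per group needed; 20 per group enrolled; 20% attrition; alpha 0.05; 80% power (the last two stated for the primary outcome only); three differences with their SDs.

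**Assumptions added.** Alpha 0.05 and 80% power carry over to these outcomes; the test is two-sided; the comparison is between two independent groups of equal size n.

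**Step 1, attrition.** 16 / 0.8 = 20 enrolled, and 20 × 0.8 = 16 completers.

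**Step 2, standardised differences** (d = difference / SD).
- BMI percentile: 1.4 / 1.5 = 0.933
- Rosenberg: 2.85 / 3.15 = 0.905
- CDI: 6.5 / 7.1 = 0.915

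**Step 3, reproduce the printed figures.** Power comes from the noncentral t distribution with 2n − 2 degrees of freedom and noncentrality d × √(n/2). Solving for 80% power at n = 20 gives d = 0.909. Multiplying by each SD:
- 1.5 × 0.909 = 1.36 (stated 1.4)
- 3.15 × 0.909 = 2.86 (stated 2.85)
- 7.1 × 0.909 = 6.45 (stated 6.5)

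In reverse, the stated differences need 19.0, 20.2 and 19.7 analysed per group for 80% power. Three outcomes on three different scales all point to 20. Reading 16 or 20 as the total for both groups (8 or 10 per group) gives power of only about 39-51%, so that reading does not fit.

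**Step 4, repeat at 16 per group.** The detectable d at 80% power becomes 1.024.

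| Outcome | Stated difference | Power at 20 per group | Power at 16 per group | Detectable at 16 (1.024 × SD) | Ratio to stated |
|---|---|---|---|---|---|
| BMI percentile | 1.4 | 82.0% | 72.4% | 1.54 | 1.10 |
| Rosenberg | 2.85 | 79.6% | 69.7% | 3.22 | 1.13 |
| CDI | 6.5 | 80.5% | 70.7% | 7.27 | 1.12 |

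The chance of missing the stated difference at 16 per group is therefore 27.6%, 30.3% and 29.3%.

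**Step 5, normal approximation.** Power ≈ Φ(d × √(n/2) − 1.96), with √(16/2) = 2.828.
- BMI percentile: Φ(2.640 − 1.960) = Φ(0.680) = 75.2%
- Rosenberg: Φ(2.559 − 1.960) = Φ(0.599) = 72.5%
- CDI: Φ(2.589 − 1.960) = Φ(0.629) = 73.5%

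The shortfall is smaller by this method but remains.

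**Step 6, one-sided test at 16 per group.** Power at the stated differences is 82.5%, 80.4% and 81.2%. The detectable d is 0.900, which gives differences of 1.35, 2.83 and 6.39.

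**The case against.** **Sidedness.** This is the strongest objection. The document says only "at an alpha level of 0.05 and 80% power", and its hypotheses are directional. A one-sided test would bring all three outcomes to 80% or more with 16 completers, and its detectable d of 0.900 is only 1% from 0.909, a small gap to resolve from rounded inputs. The objection stands as a caveat. The two-sided reading at 20 is still the likelier source, for two reasons.
- It gives 1.36, 2.86 and 6.45 against the stated 1.4, 2.85 and 6.5; the one-sided 1.35, 2.83 and 6.39 are further away on every outcome.
- Read as totals over both groups, the 80% row of Table 2 has 22 at EF = 1.25 and 16 at EF = 1.5. The two-sided t-test gives 22.2 and 16.1; the one-sided gives 17.4 and 12.6. The EF = 1.75 column (10, 12, 14) does not fit two-sided t-test totals (12.5, 13.9, 15.9), so the table is supporting evidence and not proof.

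**Power is not restated.** A reader might infer that the protocol explicitly promises 80% for these three outcomes. It does not; the 80% is carried over. But no other power level is attached to the chosen sample size, and 80% at 20 per group reproduces the figures.

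**Optional testing.** The protocol also says: "In the event that subjects decline this medical testing, they will not be excluded from participating in the MI part of the study". A reader might infer that numbers for these outcomes will fall below 16. The document does not support that. The Rosenberg scale and the CDI are questionnaires in Table 1, outside the hospital assessment. BMI is listed in that assessment, but the Randomization section has study and program facilitators helping with BMI calculation, so it is not shown to depend on the hospital visit.

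**Consequence.** The trial is sized on the CDSS, and these three figures set no sample size or decision rule. The assumed SDs are given without a source, and error in them could outweigh a 10-13% shift. This stands, and it is why severity is low.

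**Conclusion.** Wrong as written; low severity. The three detectable differences match the number enrolled, not the number that the plan expects to analyse. With 16 completers per group and a two-sided test at 0.05, power at the stated differences is about 70-72% by t-test or 73-75% by normal approximation, and 80% power needs differences about 10-13% larger.

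The conclusion rests on carrying over alpha and power from the primary calculation and on a two-sided test. If the protocol intended a one-sided test on 16 per group, power would be about 80-82.5% and only the missing statement of sidedness would remain.

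A reader might go further and infer that the trial is too small for its main question. This point gives no ground for that: the primary calculation does allow for attrition.

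**What to change.** Replace the three figures with a statement of this kind: *with 16 evaluable per group (20 enrolled, 20% attrition) and two-sided alpha 0.05, there is 80% power to detect about 1.54 BMI-percentile points (SD 1.5), 3.22 Rosenberg points (SD 3.15) and 7.27 CDI points (SD 7.1)*. If a one-sided test was intended, say so and give the figures on that basis.

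The cost is one edited sentence and three slightly less favourable figures. Recruitment, design and the primary outcome are unaffected. Keeping the present figures at 80% power would instead take 20-21 evaluable per group, or 25-27 enrolled (20 / 0.8 = 25; 21 / 0.8 = 26.25, rounded up). That is hard to justify for secondary outcomes.

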### Randomization

Once informed consent from subjects is obtained, participants will be randomly assigned to control group or treatment group based on a computer generated block randomization strategy stratified for age (10-14 and 14.1-18), and time of entry into the program (new vs. current participants). Subjects will have baseline measurements taken before randomization. At this time, a research assistant without direct contact with newly recruited participants will assign subjects to treatment or control group, based on a block randomization pattern stratified for age and program status.

Participants are unaware of the specific psychological intervention, other than "we are testing two different types of psychological support." Study and program facilitators will partially aid in the administration of some of the measures, including BMI calculation. Both the experimental and control group will be blind to which group they were randomly assigned to. Baseline measures will be administered prior to beginning therapy intervention ***(See ***Figure 2*** for a flow diagram of recruitment protocol and study procedure)*.**

**Figure 2 F2:**
[figure not shown]
**'Flow Diagram of Recruitment and Study Procedure'**.

### Statistical Analysis

Analyses will be conducted with the Statistical Analysis System (SAS). Data will be described as means with standard deviation, median with interquartile range or frequencies as appropriate. A test of randomization (unpaired Student's t-test and Fisher's exact test) will be performed to ensure that all baseline variables are equally distributed between groups.

#### Primary Analyses

The mean changes in the primary outcome, self-reported self-efficacy scores, will be conducted for each group to determine possible between-group differences. Subsequent paired samples t-tests examining treatment vs. control group differences on secondary outcomes such as weight percentile, self esteem, quality of life and depression index will also be conducted. Repeated-measures ANOVA tests will be performed to assess changes in the aforementioned outcome variables over the study period.

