### Participants

Overweight and obese youth, with BMI >85^th ^%ile for age and gender (as classified by the Center for Disease Control) [28], age 10-18 years, attending a local pediatric outpatient obesity clinic (Healthy Lifestyles Clinic) will be eligible to participate. Time of entry into the weight-loss program will also be controlled for; however, both new and current participants will have the option to participate in the study. Individuals will be excluded if they: are taking medication whose side effects may influence weight gain or weight loss, do not speak English, have known developmental delay, report being pregnant and/or report having an active eating disorder. Verbal and written consent/assent will be obtained from adolescents (and parents if under 16) at the treatment site.

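### The primary comparison of mean CDSS changes carries no baseline covariate and neither stratification factor; adjusting for them would gain precision at almost no cost

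*Protocol article*

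**What the plan says.** All references are to the protocol article.

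- **Primary outcome** (Sample Size and Outcomes): "The primary outcome for this study will be the total self-efficacy score as measured in the Child Dietary Self-Efficacy Scale (CDSS").
- **Primary comparison** (Primary Analyses): "The mean changes in the primary outcome, self-reported self-efficacy scores, will be conducted for each group to determine possible between-group differences". No test, model or covariate is named.
- **Longitudinal analysis** (same section): "Repeated-measures ANOVA tests will be performed to assess changes in the aforementioned outcome variables over the study period". Again no covariate is named.
- **Allocation** (Randomization): a "block randomization pattern stratified for age and program status", with two age bands and new versus current participants. The same section places baseline measurement before randomisation.
- **Program entry** (Participants): "Time of entry into the weight-loss program will also be controlled for". The means of control is not given.
- **Room for covariates** (Sample Size and Outcomes): in linear regression models, "this sample size would allow adjusting for 3 independent variables in addition to treatment group". The three variables are not named, and the sentence is not tied to the primary comparison.

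The only regression on self-efficacy described in full is in Exploratory Analyses. It picks the most significant correlates in order to explain variance in self-efficacy. It does not estimate the treatment effect.

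**The concern.** The design collects a pre-randomisation CDSS score and balances the arms on two factors, but the stated efficacy analysis makes limited use of either. A change score subtracts the baseline with a slope fixed at 1. A model that estimates the slope is at least as precise in large samples, and clearly more precise when r is moderate. Stratifying the allocation and then leaving the strata out of the analysis tends to give standard errors that are too large, if those factors predict the outcome.

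The trial plans for 32 completers (16 per group), so it has little precision to spare if the effect is smaller or the scores more variable than assumed. The sections on participants, randomisation and sample size all point towards covariate control, and the analysis section does not say how it enters the primary comparison.

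**Working it through.** **Inputs from the article.** Difference 1.5 units, SD 1.0, alpha 0.05 (two-sided assumed, as sidedness is not stated), 80% power, 16 completers per group, 20 after 20% attrition. Earlier studies gave a CDSS SD of 0.5 to 1.4 and a treatment change of 1.1 to 1.9. The correlation r between baseline and follow-up CDSS is not given; 0.3, 0.5 and 0.7 are assumed.

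**The plan's own figure.** The article says 16 per group "would allow the detection of between-group differences of 1.5 units with a standard deviation of 1.0". A two-sample t calculation with these inputs needs 9 per group (7 by normal approximation), and 16 per group gives 98% power, so the figure is not reproduced as stated. It comes close (15 per group) if 1.0 is the SD of the score and a change score with r = 0 is analysed, because the SD of change is then √2 = 1.41; the article does not say this. The inflation 16/(1 − 0.20) = 20 is correct. The SD is introduced as "assuming no differences between groups at baseline and a standard deviation of 1.0 (no differences between groups"), without saying whether it belongs to the score or the change. Below it is taken as the SD of the score, because the range 0.5 to 1.4 is quoted for the score.

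**Formulas, with score SD s.**

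- SD of the change: s√(2(1 − r))
- Residual SD after baseline adjustment (ANCOVA): s√(1 − r²)
- Variance ratio, ANCOVA to change: (1 − r²)/(2(1 − r)) = (1 + r)/2

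| Assumed r | Variance ratio | 32 completers are worth | Detectable difference at 80% power, s = 1.0: change → ANCOVA |
|---|---|---|---|
| 0.3 | 0.65 | 32/0.65 = 49.2 (about 17 more) | 1.21 → 0.98 |
| 0.5 | 0.75 | 32/0.75 = 42.7 (about 11 more) | 1.02 → 0.89 |
| 0.7 | 0.85 | 32/0.85 = 37.6 (about 6 more) | 0.79 → 0.73 |

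**Power at the planned values (1.5 units, s = 1.0, 16 per group).** The change score gives 93%, 98% and above 99.9% for the three values of r, and 83% at r = 0. ANCOVA gives above 99% throughout.

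**Power at the unfavourable ends of the article's ranges (1.1 units, s = 1.4, 16 per group, noncentral t).**

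| Assumed r | SD change | SD ANCOVA | Power, change | Power, ANCOVA |
|---|---|---|---|---|
| 0.3 | 1.66 | 1.34 | 44% | 62% |
| 0.5 | 1.40 | 1.21 | 58% | 70% |
| 0.7 | 1.08 | 1.00 | 79% | 85% |

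**Small-sample check.** Estimating the baseline slope multiplies the ANCOVA variance by 1 + 1/(2n − 4) = 1 + 1/28 = 1.036 on average at n = 16 per group, for normally distributed scores. The three variance ratios become 0.67, 0.78 and 0.88. Three covariates take the residual degrees of freedom from 30 to 27. With both penalties the ANCOVA powers are about 60%, 68% and 84%, so the gain shrinks slightly but remains.

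**Chance imbalance.** With 16 per group the standard error of the baseline difference is √(2/16) = 0.35 SD. A change score shifts the estimate by (1 − r) times the imbalance. At r = 0.5 and a one-standard-error imbalance that is 0.5 × 0.35 = 0.18 SD, which ANCOVA removes.

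**Stratum terms.** The documents do not say how strongly age or program status predicts CDSS, so the gain from these terms cannot be computed.

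**The case against.** The strongest reply is that the article condenses a fuller plan, names no model for the primary outcome and never calls the comparison unadjusted. Adjustment may be specified elsewhere, and stratified allocation may itself be the promised control for program entry. Both estimators are unbiased under randomisation, omitting strata is generally conservative, and power at the planned effect is already high.

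Much of this stands. There is no outright contradiction between sections, and the stated comparison is not invalid. What remains is that the article does state an analysis, mean changes plus repeated-measures ANOVA, and does not connect it to covariates that it describes elsewhere as controlled for or affordable.

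A reader might infer two stronger claims that the documents do not support:

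- *That the baseline score is ignored.* It is not. A change score subtracts it, and repeated-measures ANOVA would normally include it as a time level. The issue is a fixed rather than an estimated slope.
- *That participants with a missed visit are dropped.* Nothing in the article says so, and SAS can fit repeated measures to incomplete data. A change from baseline to month 6 needs no month 12 value. Only if the ANOVA is run in its classical complete-case form over three visits would month 6 data be lost. At most, if all of the planned 20% attrition fell after month 6, that analysis would use 16 rather than 20 per group at month 6, with a standard error √(20/16) = 1.12 times as large.

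**Conclusion.** The point holds as an inefficiency and a loose end between sections; it is not an error that biases the result. Baseline adjustment would cut the variance of the primary comparison by about 35%, 25% or 15% for r of 0.3, 0.5 or 0.7, in large-sample terms. The practical effect is small at 1.5 units and SD 1.0. It is material at 1.1 units and SD 1.4, where power rises by about 18, 12 or 6 percentage points before the small-sample penalty.

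These figures rest on the assumed r, on reading the article's SD as that of the score, on equal SDs at baseline and follow-up, and on treating the low end of the reported treatment change as a between-group difference, in line with the plan's use of the midpoint, (1.1 + 1.9)/2 = 1.5. No size can be put on the benefit of the stratum terms. Because the improvement uses only data already collected, it should be made.

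**What to change.** State one model for the primary comparison: CDSS total score on arm, baseline CDSS, age stratum and program status. Two forms would serve:

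- ANCOVA of the month 6 score; or
- a likelihood-based mixed model in SAS over months 6 and 12, with visit and arm-by-visit terms, using every observed post-baseline value and reporting the arm difference at month 6.

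The Primary Hypotheses name both 6 and 12 months, so the text should say which visit is primary. Baseline, age stratum and program status make three covariates, which fits the number the sample size section says is affordable. One sentence each in Participants, Randomization and Sample Size and Outcomes should then point to this model. If a full analysis plan already contains it, citing that plan is enough.

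For secondary outcomes, use the same covariate approach with each outcome's own baseline, at whichever visits that outcome is measured. The metabolic tests need care: the Assessment and testing section and the Appendix place them only at the start and end of the study, so a model over two follow-up visits may not apply.

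The cost is wording, three residual degrees of freedom for the ANCOVA, and a few more parameters for the mixed model. No extra participants, visits or measurements are needed.

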Participants who consent to receiving therapy in addition to their usual care will be randomly assigned to one of two therapies: Motivational Interviewing (experimental arm) or social skills training (control arm). Social skills training will be conducted using a standardized treatment manual, appropriate for this age range. Sessions are based around finding appropriate ways to navigate typical social situations (e.g., how to negotiate with parents). For the MI treatment group, a clinical psychology doctoral student trained in Motivational Interviewing will administer approximately six individual motivational interviewing treatment sessions approximately 30 minutes in length. Sessions will be tape recorded and a percentage (approximately 25%) coded by coders trained in the Motivational Interviewing Treatment Integrity Code (MITI). A smaller percentage (approximately 5%) of the control group sessions will also be randomly checked by a trained MINT trainer to ensure that MI is not being conducted with the control group. While the MI literature indicates that certain methodological parameters (e.g., optimal number of treatment sessions) have not been established, studies have shown that six MI sessions can effect significant behavioral changes in adolescents [29]. The current MI treatment will take place at the Toronto East General Hospital, in a private room. To assess the validity of treatment implementation, experts trained in MI outside of the study, will independently and randomly review and rate approximately 25% of recorded therapy sessions. This will serve as a manipulation check.

The control group will receive six sessions of social skills training. Sessions will be matched for session frequency and duration. This administrator will not be trained in motivational interviewing. These sessions will also be audio taped and reviewed by an MI expert to verify that MI techniques have not been used.

All therapy sessions will take place over the course of 6 months, and will occur at the time of the client's regular follow-up visits to the treatment site (≈ once per month). Therefore, clients will not be required to attend sessions in addition to their regularly scheduled appointments. Consenting participants will spend their usual time with the dietitian as per regular follow-up protocol, and an additional 30 minutes with the therapy provider.

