**Figure 1 F1:**
[figure not shown]
**'Theoretical Model of Hypotheses to be Tested'**.

**H**_**o **_**2**: At conclusion of the intervention (6 months) and 12 month follow-ups, in comparison to the control group, the MI Group will report higher levels of healthy behaviors (i.e., increased activity as measured by the Weight Loss Behavior Scale [32] and the Dutch Eating Behavior Questionnaire [33]).

**H**_**o **_**3**: At conclusion of the intervention (6 months) and 12 month follow-ups, in comparison to the control group, the MI group will demonstrate increased improvement in psychological functioning as measured by the Peds Quality of Life questionnaire [34], the Child Depression Inventory [35] and the Rosenberg Self-Esteem Scale [36].

**H**_**o **_**4**: At conclusion of the intervention (6 months) and 12 month follow-ups, in comparison to the control group, the MI group will demonstrate improved physiological functioning/decreased metabolic risk as indicated by changes in BMI, body composition, improved lipid profile, insulin resistance, blood pressure and fitness;

**H**_**o **_**5**: Improvements in behavior change and self-efficacy will correlate with reduction in BMI and improved metabolic status.

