## Discussion

Results from this study are hoped to enhance our understanding of the efficacy of MI with children and adolescents who are overweight or obese. If findings suggest that MI effects positive change to the treatment group over and above the control group intervention, and this correlates to improvement in psychological and physiological health, MI may have wider clinical applications. For example, the results of this study may generalize to other overweight and obese children and adolescents. External validity may be limited by participant demographics such as ethnicity, baseline obesity severity or comorbid diagnoses of weight related disorders such as diabetes, such that the results may not generalize to participants with characteristics that were not well represented in the study. Although attempts will be made to recruit participants of all ethnicities and participants will be matched for age and gender, certain types of participants may be underrepresented. Similarly, the results may not generalize beyond adolescents who are willing to volunteer for research or were motivated by the incentive of weight loss offered for participation. Another possible imitation to our study is the exclusion of parents. Future studies could include MI intervention with youth and their parents.

Health-related problems that accompany obesity are of great concern in the obese pediatric and adolescent population. Youth who are overweight have two to four times increased odds of having low scores for psychological health, self-esteem, and physical functioning [39]. Taken together, it is important that researchers develop empirical psychological interventions, grounded in theory, that will extend obesity treatment from support and education to promote sustained behavior change. As such, if significant results are found, Motivational Interviewing may be acknowledged as an effective treatment modality for child and adolescent obesity.

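### Paired-samples t-tests are named for treatment-versus-control differences on secondary outcomes, although the two arms are independent randomised groups

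*Protocol article*

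**What the plan says.** All references are to the protocol article.

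- **Primary Analyses:** "Subsequent paired samples t-tests examining treatment vs. control group differences on secondary outcomes". Four outcomes follow as examples: weight percentile, self-esteem, quality of life and depression. The next sentence adds: "Repeated-measures ANOVA tests will be performed to assess changes in the aforementioned outcome variables over the study period".
- **On-site therapy intervention and Randomization:** consenting participants are individually randomised to MI or social skills training, "based on a block randomization pattern stratified for age and program status". Gender is not a factor, and no step forms matched pairs.
- **Discussion:** "participants will be matched for age and gender".
- **Statistical Analysis, opening paragraph:** "A test of randomization (unpaired Student's t-test and Fisher's exact test) will be performed", to compare the same two groups at baseline.
- **Primary Hypotheses, H3:** "in comparison to the control group, the MI group will demonstrate increased improvement in psychological functioning", at 6 and at 12 months. H4 makes the same kind of comparison for BMI and metabolic measures.

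**The concern.** A paired t-test needs a defined partner for every observation. In this design a participant's only natural partner is their own earlier measurement; nobody in the MI arm has a partner in the control arm. An analyst who follows the sentence therefore has two options, and neither is a sound test of the hypotheses:

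1. **Pair across arms.** The pairs must be invented. The test cannot be run on everyone if the arms end with different numbers, and with 20% attrition expected they may. The p-value also changes with the order of the records.
2. **Pair within arms, before against after.** This tests whether each arm changed, whereas H3 and H4 ask whether MI changed more than control. Both arms receive dietitian counselling, monthly sessions and telephone check-ins, so change in both is plausible.

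At stake is the between-arm evidence on the named psychological outcomes (H3) and on weight (H4). There is also room to choose between two different analyses once the data are seen.

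**Working it through.** **Inputs from Sample Size and Outcomes.** 20 per group, which is 16 inflated for 20% attrition (16 / 0.8 = 20). Detectable differences and SDs: BMI percentile 1.4 and 1.5; Rosenberg 2.85 and 3.15; CDI 6.5 and 7.1. Alpha is 0.05. Two-sided testing is assumed, and the 80% power is carried over from the primary calculation.

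**Step 1: reproduce the plan's secondary figures.** For two independent groups, d = difference / SD, and the noncentrality is d × √(n/2) on 2n − 2 degrees of freedom. For n arbitrary cross-arm pairs, the SD of a difference is √2 × SD. The noncentrality is then the same, but the degrees of freedom fall to n − 1.

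| Outcome | d | Unpaired, 20 per arm | 20 arbitrary pairs | 20 pairs, stated SD read as SD of the paired difference |
|---|---|---|---|---|
| BMI percentile | 1.4/1.5 = 0.933 | 82.0% | 79.9% | 97.7% |
| Rosenberg | 2.85/3.15 = 0.905 | 79.6% | 77.5% | 97.0% |
| CDI | 6.5/7.1 = 0.915 | 80.5% | 78.4% | 97.3% |

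The unpaired test needs 19.0, 20.2 and 19.7 per arm for 80% power, which matches 20 per arm. The stated SDs were clearly not used as SDs of paired differences. The figures cannot sharply separate an unpaired test from arbitrary pairing, because those two differ only in degrees of freedom.

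**Step 2: cost of pairing across arms.** With 16 completers per arm, the degrees of freedom fall from 30 to 15 and the critical t rises from 2.042 to 2.131. Power moves from 72.4% to 69.4% (BMI percentile), 69.7% to 66.7% (Rosenberg) and 70.7% to 67.8% (CDI). In 100,000 simulated null trials, random pairing gave a type I error of 5.0%.

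**Step 3: the within-arm reading.** Assume both arms have the same true change δ, in units of the SD of change. Each arm's paired test with n = 16 has noncentrality δ√16 = 4δ on 15 degrees of freedom. Let p be its power. The arms are independent, so the chance that MI is significant and control is not is p(1 − p).

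| δ (assumed) | 4δ | p | p(1 − p) |
|---|---|---|---|
| 0.3 | 1.2 | 0.203 | 0.203 × 0.797 = 0.162 |
| 0.5 | 2.0 | 0.465 | 0.465 × 0.535 = 0.249 |
| 0.8 | 3.2 | 0.848 | 0.848 × 0.152 = 0.129 |

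Simulation agrees (16.1%, 24.9%, 12.8%). With 20 per arm it gives 18.7%, 24.5% and 7.0%. A valid two-sided between-arm test would falsely favour MI in 2.5% of trials.

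**The case against.** The best defence is that this is a slip of one word. The same groups are compared at baseline with an unpaired test, the secondary detectable differences fit unpaired comparisons, and the sentence itself speaks of differences between groups. That is probably right about intent. It does not correct the text, which states a wrong test rather than leaving one open for a fuller analysis plan to supply.

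Second, other analyses are planned. A repeated-measures ANOVA covers the same outcomes and would give a valid arm comparison through a group-by-time term. The sample size section also foresees a regression with treatment group and three further variables. This stands as mitigation, so one cannot say that H3 and H4 depend on the paired tests alone. But no group-by-time term is stated, and the outcome of the regression is not named.

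A reader might infer more than the document supports:

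- *That every secondary outcome is affected.* The sentence gives four examples. The other H4 measures, such as lipids, blood pressure and fitness, are not named in it. The primary self-efficacy outcome is not assigned this test either.
- *That the error rate is inflated whichever way the sentence is read.* Random cross-arm pairing keeps about 5%. Its faults are undefined pairs, dependence on record order and about three points of lost power.
- *That 13% to 25% is the plan's false-positive rate.* It applies only if the tests are run within arms and benefit is claimed when MI alone is significant. The plan states neither.

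The Discussion's remark about matching might seem to supply the pairs. Randomization contains no matching and no gender factor, so the remark is a second inconsistency.

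**Conclusion.** The point holds as a misstated test. A paired-samples t-test does not fit a treatment-versus-control comparison of two independent randomised arms, and the document's own baseline test and secondary sizing are consistent with unpaired comparisons.

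The consequence depends on how the sentence is carried out. Across arms, the cost is small in power, but the result is arbitrary. Within arms, followed by a comparison of significance, MI alone would be significant in about 16%, 25% or 13% of trials with no true difference between arms. Those figures rest on 16 completers per arm, two-sided 0.05, independent arms, equal true changes of 0.3, 0.5 or 0.8 SD of change (assumed, not taken from the document) and the unstated decision rule. The repeated-measures ANOVA would limit the damage if its group-by-time term were specified. The sentence should be corrected before any analysis.

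**What to change.** - In Primary Analyses, replace the paired-samples t-tests with a between-group comparison of each secondary outcome at both 6 and 12 months, since H3 and H4 name both times. An unpaired t-test on change from baseline is the minimum.
- Better is ANCOVA of the follow-up value on arm, baseline value, age stratum and program status. That is treatment group plus three variables, which is the number the sample size section says the trial can support. The repeated-measures model with an explicit group-by-time term is an acceptable alternative.
- Name one of these as the analysis that decides each hypothesis.
- In the Discussion, replace the statement about matching for age and gender with randomisation stratified by age and program status.

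The cost is one sentence in each of two sections. Changing the test calls for no change in sample size, because the secondary detectable differences already fit an unpaired comparison with 20 per arm.
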